## Abstract

**Background:**

Neuropathic pain (NP), a complication of several conditions (eg, diabetic neuropathy and varicella zoster), is a common challenging problem, and there is a growing need to develop safe and effective nonopioid treatments. Sleep disturbance is commonly associated with NP because pain intensity in NP conditions is often worse at night. The pineal hormone melatonin has been shown to reduce pain in both preclinical and clinical settings, in addition to multiple trials demonstrating efficacy for primary insomnia and delayed sleep phase syndrome.

**Objective:**

We propose to conduct a clinical trial to evaluate the efficacy and safety of melatonin for NP.

**Methods:**

Using a double-blind, placebo-controlled, crossover design, 30 adults with NP will be randomly allocated to one of two sequences of treatment with melatonin and placebo. During each of the two treatment periods, participants will take capsules containing melatonin or placebo for 4 weeks, followed by a 7-day washout period. The primary outcome will be mean daily pain intensity (scored 0-10) at maximally tolerated doses (MTDs) during each period. Secondary outcomes, assessed at MTDs, will include global improvement, adverse events, mood, and quality of life.

**Results:**

This trial was registered in the International Standard Randomized Controlled Trial registry May 4, 2022 (ISRCTN #16215617), attained conditional ethics approval May 9, 2022 (Queen’s University Health Sciences & Affiliated Teaching Hospitals Research Ethics Board protocol number ANAE-387-22), and recruitment is set to start August 2022.

**Conclusions:**

This trial will provide rigorous evidence comparing the efficacy of melatonin to that of placebo in the treatment of NP.

**Trial Registration:**

ISRCTN Registry 16215617; https://www.isrctn.com/ISRCTN16215617

**International Registered Report Identifier (IRRID):**

PRR1-10.2196/40025

## Introduction

Neuropathic pain (NP) is a common form of secondary chronic pain due to a lesion or disease of the nervous system [1] such as diabetic neuropathy, spinal radiculopathy, HIV-neuropathy, postherpetic neuralgia, and cancer-related conditions [2]. NP has been estimated to have a prevalence of 7%-8% [3] and is known to impair physical, social, and occupational function with a subsequent devastating impact on patients, their families, and society [4,5]. Oral medications may be a valuable element of multimodal NP management owing to their ease of administration and engagement of drug effect sites throughout the sensory nervous system [6,7]. However, studied treatments provide only partial benefit owing to incomplete efficacy and dose-limiting adverse effects (AEs) [8].

Chronic pain, including NP conditions, is commonly associated with sleep disturbance. Complex interactions between pain and sleep are such that effective therapy requires coordinated attention to the interaction between pain and sleep [9,10]. In patients with chronic pain, observations suggest that a night of poorer sleep is followed by a more painful day, and a more painful day is followed by a night of poorer sleep [11]. Thus, in addition to treating one of the most prominent secondary features of chronic pain, pain therapies that also improve sleep may be expected to have more favorable efficacy [12].

Melatonin (N-acetyl-5-methoxytryptamine), a hormone secreted by the pineal gland, has been implicated in several homeostatic functions including sleep, modulation of circadian rhythms and mood, enhanced immunity, and antioxidant free radical scavenging [13]. Relevant to pain, accumulating preclinical and clinical evidence suggests antinociceptive effects of melatonin by acting on MT_1_ and MT_2_ membrane receptors (to reduce cyclic AMP) but possibly also (1) by indirectly activating opioid receptors, (2) by inhibiting the production of proinflammatory cytokines, (3) by activating γ-aminobutyric acid-A receptors, and (4) through its antioxidant effects [14]. Emerging evidence suggests that melatonin reduces pain in both preclinical and clinical (fibromyalgia) settings [15-17], in addition to multiple randomized controlled trials (RCTs) demonstrating efficacy for primary insomnia and delayed sleep phase syndrome [18]. After oral administration, melatonin undergoes first-pass hepatic metabolism [19], with subsequent secondary renal metabolism and elimination [20]. A review of studies involving varying doses [21] reported that oral administration of melatonin results in a transport maximum ranging 15-210 minutes, and a half-life ranging 28-126 minutes [21].

Thus, in the interest of further evaluating the analgesic efficacy of melatonin for NP, our objective is to conduct a double-blind RCT to compare the efficacy of melatonin to that of placebo in patients with chronic neuropathic conditions.

## Methods

### Ethics Approval

This study has been submitted to, and is currently under review by, the Queen’s University Health Sciences & Affiliated Teaching Hospitals Research Ethics Board (protocol #ANAE-387-22). This study protocol will be conducted in accordance with the principles of the Declaration of Helsinki, Initiative on Methods, Measurement, and Pain Assessment in Clinical Trials’ guidelines [22,23], and in accordance with the International Council for Harmonisation Good Clinical Practice: Consolidated guideline. This trial has been funded by the Physicians’ Services Incorporated Foundation and was registered in the International Standard Randomized Controlled Trial Registry on May 4, 2022 (ISRCTN #16215617).

### Aims and Hypothesis

The objective of this trial is to evaluate the efficacy, safety, and tolerability of melatonin in treating pain in participants with chronic neuropathic conditions. Our primary hypothesis is that melatonin is safer than and superior to placebo and is well tolerated in treating neuropathic pain.

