### Outcome Measures

During the trial, the study nurse will contact participants by telephone at least once a week to evaluate adverse effects, assess pain intensity, and encourage compliance. Furthermore, participants will be evaluated at the clinic on 1 of the 5 weekdays of week 4 of each treatment period for vital signs and assessment of secondary outcomes. Finally, participants will be followed up by telephone 2 weeks and 3 months following the completion of the study to document any subsequent problems or adverse events. Table 1 shows the schedule of study assessments.

The primary outcome is the mean daily “average” pain intensity [28] experienced while on the MTD of melatonin or placebo during week 4 (days 22-28). This will be determined from participants’ ratings of their “average pain over the last 24 hours” completed in patient diaries every morning using a numerical rating scale from 0 to 10. Given the potential circadian variability of pain intensity [29], clinical trial methods have involved the following: (1) requiring participants to rate their pain multiple times through the day or evening [26,27], which increases participant burden and may adversely affect participant retention or missing data or (2) requiring participants to provide a retrospective rating of their “average pain over the last 24 hours” [30], which may be susceptible to recency bias. Based on our experience, we are proposing the latter approach, although both approaches have led to valid and generalizable trial results in clinical pain trials. Secondary outcomes include frequency or severity of treatment-emergent AEs; scores on the Neuropathic Pain Symptom Inventory [31], Medical Outcomes Study Sleep Scale [32], Patient Global Impression of Change [33], Brief Pain Inventory [34], Beck Depression Inventory-II [35], Beck Anxiety Inventory [36], the short-form McGill Pain Questionnaire [37], the SF-36 survey [38], and blinding questionnaires; and acetaminophen consumption. All these outcomes will be assessed at baseline and during week 4 of each treatment period, except for AEs and acetaminophen consumption, which will be assessed weekly during each treatment period.

**Table 1 table1:** Schedule of study assessments.

Assessments	Screen	Baseline	treatment periods				3-month posttrial completion
			First 3 weeks of treatment	Fourth week of treatment	Washout		
Days per treatment period >	–14	–7	1-21	22-28	29-35		
Present pain intensity (scale 0-10; average and worst)	✓						

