### Sample Size

Statistical considerations underlying this sample size calculation are based on the null hypothesis that there is no difference in pain intensity between the study treatments and the alternative hypothesis that melatonin is different from placebo. Systematic reviews of placebo-controlled chronic pain trials consistently reveal that significant differences between treatment and placebo groups vary between 0.5 and 1.5 points, depending on the magnitude of the placebo response in any given trial [22]. Thus, based on a previous estimated within-participant variation of 2.5 from studies on NP [26], we project that a sample size of 21 participants would allow for an 80% chance of detecting (α=.05) a mean treatment group difference of 1.5 points on a 0-10 numerical rating scale. In order to have a sample size divisible by 4, we have adjusted the sample size to 24 participants. Accounting for trial dropout rates from our previous trials and for a 2-period crossover design, we expect that the recruitment of 30 enrollees for each trial will yield the aforementioned number of completers.

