### Statistical Analysis

Participants who complete both treatment periods will be included in trial analyses. When data from only one period are available, sensitivity analysis including all participants will also be performed, by assuming some reasonable but extreme values for the remaining periods. Those receiving at least one dose of study drug will be included in the safety analyses. The primary outcome will be calculated as an average of pain scores as recorded in the participant pain diaries within the last 7 days (at MTD in week 4 of the treatment), if more than 50% of the information (at least 4 days) is not missing [39]. Otherwise, mean daily pain will be treated as missing data. Sensitivity analyses based on the average of all available pain scores will also be performed to confirm the results of the primary analysis. A linear mixed model with sequence, period, treatment, and the first-order carryover effects as fixed effects and participant as a random effect [39] will be used to test whether there is any treatment difference among groups and to estimate the least squares mean of the mean daily pain intensity for each treatment group, adjusting the carryover and period effects. The comparison between melatonin and placebo will be performed on the basis of the least squares means and SDs from the linear mixed model. Sensitivity analyses will be performed using a pattern-mixture model [40] based on patterns of missing data to check the robustness of results in case data may not be missing at random.

Secondary outcomes will be analyzed similarly except that (1) only 1 measurement will be analyzed in the last week for the singular measures (ie, final week questionnaires), and (2) the scoring algorithms developed for the Brief Pain Inventory, the Beck Depression Inventory-II, the Beck Anxiety Inventory, and the SF-36 will be first used to derive the subscales or domains within these instruments, and the scores on these subscales or domains will be used as response variables in the linear mixed model analysis.

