## Discussion

NP remains a challenging condition to treat, with current recommended pharmacological therapies providing only partial relief from pain, sometimes exacerbating other symptoms [41]. To the best of our knowledge, this proposed RCT is the first to investigate the safety and efficacy of melatonin for the treatment of NP. Given the potential improvement of pain and sleep with melatonin, we expect to observe a significant difference between the melatonin and placebo groups with respect to the primary outcome of pain and the secondary outcome of sleep in patients with NP. Although there has been some previous interest in the use of melatonin for pain management, few trials have been conducted in clinical chronic pain, and most of these have involved participants with fibromyalgia [15-17] and only one trial involved participants with NP [42]. Therefore, we expect that this trial will provide much needed evidence to further guide the appropriate use of melatonin in the management of NP.

Potential threats to this trial include challenges with patient recruitment, early dropouts, noncompliance, and protocol violations. However, the planned study design as well as our experience with similar previous chronic pain trials will mitigate these threats. In particular, careful and frequent follow-up of trial participants, timely management of treatment-emergent AEs, and open communication between participants and trial personnel are, once again, expected to minimize trial dropouts and thus maximize participant retention. Furthermore, as with our past RCTs, noncompliance, protocol violations, and early dropouts will be minimized by our proposed crossover design, thorough study participant teaching, and close weekly follow-up of participants. Variations in melatonin bioavailability across trial participants may increase the overall variability in trial results; however, compared to a parallel-group trial, our proposed crossover design will reduce the impact of such variability, whereby each participant acts as their own control.

In light of the current lack of desperately needed new improved NP therapeutics, this trial is expected to provide evidence for a safer and more effective treatment for NP. The development of this proof-of-concept RCT of melatonin in NP will facilitate future confirmatory RCTs and the implementation of melatonin into practice.

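### The primary hypothesis claims melatonin is safer than placebo, but the primary outcome, test hypotheses and sample size cover pain only, and the blanket rule for secondary outcomes does not suit non-continuous data

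*Protocol article*

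**What the plan says.** Aims and Hypothesis in the protocol article joins three claims in one primary hypothesis: "Our primary hypothesis is that melatonin is safer than and superior to placebo and is well tolerated in treating neuropathic pain".

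The other sections treat pain alone as primary:

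- **Outcome Measures** names one primary outcome, the mean of the daily average-pain ratings in week 4. Adverse events come under a different label: "Secondary outcomes include frequency or severity of treatment-emergent AEs". Patient Global Impression of Change and the blinding questionnaires are in the same secondary list.
- **Sample Size** sets out the two hypotheses behind the calculation: "null hypothesis that there is no difference in pain intensity between the study treatments and the alternative hypothesis that melatonin is different from placebo".
- **Statistical Analysis** specifies a linear mixed model compared on least squares means for the primary outcome, then says "Secondary outcomes will be analyzed similarly except that" two exceptions apply. The first is that final-week questionnaires contribute a single measurement. The second is that four named instruments are scored into subscales, which then become response variables in the linear mixed model. The section also defines a safety population of everyone with at least one dose, but attaches no endpoint or method to it.

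**The concern.** A primary hypothesis should correspond to a primary outcome, a test and a sample size. The pain part does. The part saying melatonin is safer than placebo does not, and it is a superiority claim, so it would need a defined safety measure and a comparison able to show a difference in melatonin's favour. As written, the headline claim of the trial is wider than what the trial is set up to answer, and a reader of the results could not tell what would count as confirming or refuting it.

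The second, lesser concern is the blanket rule for secondary outcomes. Neither exception changes the model for adverse events, global impression of change or blinding guesses. Taken at its word, the rule compares Gaussian least squares means for outcomes that are sparse events, ordered categories or nominal guesses, in 24 to 30 people.

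**Working it through.** **1. Does any safety quantity enter the sample size?**

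Inputs from Sample Size: "80% chance of detecting (α=.05) a mean treatment group difference of 1.5 points on a 0-10 numerical rating scale", and "based on a previous estimated within-participant variation of 2.5 from studies on NP". The article does not say whether 2.5 is a standard deviation of differences, a within-participant standard deviation or a variance. Taking it as the standard deviation of within-participant differences, with two-sided α:

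n = [SD × (z₀.₉₇₅ + z₀.₈₀) / δ]² = [2.5 × (1.960 + 0.842) / 1.5]² = 21.8, so 22.

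This is within one of the stated 21. The exact paired t calculation gives 24, and 24 completers have 80.4% power. Recruitment of 30 matches 24 / (1 − 0.20) = 30, an implied 20% dropout. The stated numbers are thus accounted for by pain inputs alone. No adverse event rate, difference or margin appears.

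**2. The hypothesis beside the plan that should test it**

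| Part of the primary hypothesis | Primary outcome | Null and alternative | Sample size | Stated method |
|---|---|---|---|---|
| Superior to placebo (pain) | Week-4 mean daily pain | Yes | Yes | Linear mixed model |
| Safer than placebo | None | None | None | Population only; otherwise the general rule for secondary outcomes |
| Well tolerated | None | None | None | As above |

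The mismatch lies between sections of the same document. It does not depend on detail left to another one.

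**3. What could a trial of this size show about being safer?**

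The article gives no adverse event rates, so these are assumptions. Let P and M be the proportions with an event on placebo and on melatonin. With independence within participant, the discordant probabilities are a = P(1 − M) (placebo only) and b = M(1 − P) (melatonin only). Power is that of the exact two-sided 0.05 McNemar test, counting only results favouring melatonin. The number of discordant pairs is binomial(n, a + b), and the placebo-only share of them is binomial with probability a/(a + b). Pairs needed for 80% power:

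n = [1.960·√(a + b) + 0.842·√((a + b) − (a − b)²)]² / (a − b)²

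Example, 30% against 10%: a = 0.27, b = 0.07, a + b = 0.34, a − b = 0.20. Then (1.960 × 0.583 + 0.842 × 0.548)² / 0.04 = 64.3, so 65.

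| Placebo vs melatonin (assumed) | Power, n = 24 | Power, n = 30 | Pairs for 80% |
|---|---|---|---|
| 20% vs 10% | 6% | 10% | 202 |
| 30% vs 20% | 6% | 8% | 296 |
| 30% vs 15% | 13% | 18% | 124 |
| 30% vs 10% | 26% | 36% | 65 |
| 40% vs 30% | 6% | 8% | 359 |
| 40% vs 20% | 21% | 28% | 84 |
| 50% vs 25% | 31% | 41% | 61 |

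Independence matters here. At the other extreme, where every participant with an event on melatonin also has one on placebo, power runs from 3% to 58% at n = 24 and from 7% to 80% at n = 30. The 80% needs event rates to halve from 50%, with maximal correlation and all 30 contributing both periods.

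**4. The rule for secondary outcomes**

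Adverse events, global impression of change and blinding questionnaires are all listed as secondary, and neither exception changes their model. The fit then differs by outcome:

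- *Blinding guesses.* These are nominal. The article does not give the response options. If they include an unsure category, a mean of the codes depends on how the categories happen to be numbered and has no meaning.
- *Adverse events.* With few events in 24 to 30 people, normal-theory intervals for a difference in means are unreliable.
- *Global impression of change.* This is ordinal. Treating the score as numeric is a common convention, so the objection is weakest here.

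**The case against.** The strongest defence is that the operative plan is already about pain. The abstract, Outcome Measures, Sample Size and the primary model all agree, and no α or success criterion attaches to safety, so the loose sentence changes no test, error rate or sample size. That stands, and it limits the consequence. It does not remove the contradiction, because the sentence is labelled the primary hypothesis and no separate analysis plan would alter it.

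The second defence is that the routing of adverse events into the linear mixed model is inferred. Statistical Analysis names that model explicitly only for the primary outcome and the four scored instruments, and it mentions separate safety analyses with their own population. That also stands. The literal reading is available because adverse events are listed as secondary outcomes, but it is not certain, and a statistical analysis plan that is not shown may set other methods.

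A reader might infer four stronger things that the documents do not support:

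- *That no valid safety test exists.* Only the article is at hand; what can be said is that it states none.
- *That a non-significant adverse event comparison would confirm part of the primary hypothesis.* The claim is one of superiority, and a non-significant result cannot confirm that.
- *That the Discussion's expectation that "this trial is expected to provide evidence for a safer and more effective treatment for NP" is a planned test that fails for want of an active comparator.* It is an aspiration, and the same paragraph calls the trial proof-of-concept and defers to later confirmatory trials.
- *That the zero-event bound, 1 − 0.05^(1/30) = 9.5%, shows comparative safety cannot be established.* It bounds one event rate on one treatment and says nothing about a paired difference.

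**Conclusion.** The point holds as an internal contradiction. The stated primary hypothesis includes being safer than placebo, while the primary outcome, the null and alternative hypotheses and the sample size concern pain only, and the article states no safety endpoint, margin or test that could support the claim. This conclusion needs no assumption about adverse event rates.

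The power figures only illustrate scale. They rest on assumed rates, a yes/no event per period and a McNemar comparison. Within those assumptions, 24 to 30 participants would usually be far too few to show fewer events on melatonin.

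The analysis-rule part is secondary and conditional on reading the rule literally. It is firm for nominal blinding guesses with more than two options, reasonable for sparse adverse events and weak for global impression of change. The primary pain analysis is not affected by either part. The change should be made because a headline claim is otherwise unsupported and the repair is cheap.

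**What to change.** 1. **Aims and Hypothesis.** Restrict the primary hypothesis to a difference in week-4 mean daily pain between melatonin and placebo. Delete the claim of being safer than placebo. State safety and tolerability as secondary objectives, reported by estimates with confidence intervals.
2. **Statistical Analysis.** Limit the rule on similar analysis to continuous secondary outcomes and exempt the rest:
   - Adverse events: counts and proportions by treatment received in everyone with at least one dose. Add a within-participant comparison, for example Mainland-Gart with an exact confidence interval, in those with data from both periods. Participants with one period cannot enter the paired comparison, so the two sets must be named separately.
   - Blinding guesses: categorical summaries per period, for participants and for the study nurse.
   - Global impression of change: say whether it is analysed as ordinal or deliberately treated as a numeric score.

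The cost is a few sentences, standard categorical summaries and a more modest safety claim. Sample size, randomisation and data collection do not change. If the investigators want to keep the safer-than claim as primary, they would have to define a safety endpoint and size the trial for it, which is a different trial.
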